**Fig. 1 Fig1:**
[figure not shown]
CONSORT (Consolidated Standards of Reporting Trials) flow diagram. IHCA: In-hospital Cardiac Arrest; ECMO: Extracorporeal Membrane Oxygenation; VAD: Ventricular Assistance Device

### Data collection

Data will be collected, verified, and uploaded to a protected electronic web-based database (Xolomon) by their designated site coordinators/investigators under the oversight of their IRB. Database has been designed following the Utstein model [19]. Database is hosted according to European legislation regarding patient data protection. It is drafted in English and Spanish.

Variables recorded will include hospital characteristics, the resuscitation team, patient’s demographics and background, CPR, post-resuscitation care, mortality, survival and long-term evolution (see Table 1).

**Table 1 Tab1:** Description of variables collected in database

Hospital characteristics: level of care; existence of cardiac arrest management plan; rapid response team: existence and composition; early warning scores
Patient demographics and characteristics: patient data before cardiac arrest (age, sex, weight, height, baseline neurological assessment, medical history, previous treatments)
Description of cardiac arrest: date and time; cause of arrest; place of arrest; cardiac rhythm; contributing factors
Description of cardiopulmonary resuscitation: resuscitation team (team members, number of providers, background); ventilation (airway management, ventilation objectives), chest compressions (rate, depth, synchrony, feedback device); defibrillation (shocks, energy); drugs (adrenaline, amiodarone, lidocaine, calcium, bicarbonate, fluids, others); quality control (invasive blood pressure, end tidal CO2); other treatments (ECMO, POCUS, drainage); time to ROSC; CPR ending; CPR complications; survival; cause of death
Post-resuscitation care: hemodynamic care (blood pressure, drug support, cardiac rhythm); ventilatory support (mechanical ventilation, ventilation parameters, oxygenation, blood gases results); neurological examination (BIS, pupils, Glasgow coma scale, POPC); renal support treatment; metabolic parameters; temperature control management
Outcomes: length of PICU and hospital stay; neurological outcome at discharge (POPC, Glasgow coma scale)
Long term follow-up: brain image (MRI, CT scan, EEG); neurological examination

### Outcomes assessment

The primary outcome is survival at hospital discharge. Secondary outcome being survival with favorable neurological status. Analysis of different factors influencing both outcomes will be performed.

### Statistical analysis

Data analysis plan: The data will be manually reviewed for errors, missing data and outliers before analysis. Extreme values will be set to missing if they are deemed unlikely, based on their validity range. Descriptive analysis of the data will be reported. Continuous variables will be reported as either median and interquartile range (IQR) or mean and standard deviation (SD) based on the distribution. Categorical var﻿iables will be described in numbers, percentages or both.

### Sample size

As this is an observational study with no intervention, we have not conducted a power calculation. Based on previous studies [3], we estimate that we will enroll at least 250 to 300 eligible cardiac arrest events. This would represent a large international dataset of pediatric cardiac arrest data with significant power to enable exploration of important correlations between performance and survival through multivariate analysis.

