## Study aims

The objective of PACHIN is (1) to study the relationship between the characteristics of cardiopulmonary resuscitation (CPR) and outcomes, focusing on the influence of ventilation parameters (intubation or not during resuscitation and controlled or uncontrolled ventilation) on the recovery of spontaneous circulation, survival, and short- and long-term neurological prognosis of children with in-hospital cardiac arrest. (2) To study the relationship between post-resuscitation measures (especially ventilation, oxygenation, blood pressure, analgosedation and temperature) with survival and short- and long-term neurological prognosis in children with IHCA. (3) To create a permanent register of pediatric in-hospital cardiac arrest for European and Latinamerican countries.

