### Patient elegibility

Inclusion criteria: all children aged 1 month to 18 years who suffer a CA in hospital. For the study, CA is defined as the absence of vital signs requiring at least one minute of chest compressions. Subsequent episodes of CA may be included for the same individual.

Exclusion criteria: Patients being treated with extracorporeal circulatory support (ECMO or ventricular assistance) at the time of CA. Patients who suffer a cardiac arrest and require ECMO for ROSC, after performing conventional CPR, will not be excluded. Duration of the data collection period 24 months.

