## Limitations

The main limitation of the study is that patient recruitment cannot be planned because CA is an unexpected sudden event. On the other hand, when CA happens, all attention is driven towards CPR, so it might be difficult to record all data related to the characteristics of CPR while performing it. Another limitation of the study is that the final results of CPR are influenced by many variables and it can be very difficult to differentiate the isolated effect of each factor. Furthermore, recording as many variables as aimed per CA requires a lot of dedication and careful review and supervision of each case by the study coordinator. Being CA a rare event in pediatric patients, it might be difficult to find statistically significant differences in some parameters such as mortality. Thus, the participation of a significant number of hospital centers and collaborating researchers is necessary. This is one of the fundamental reasons for a multicenter study. Finally, the neurological follow-up at one year of some patients will end after the end of the study period.

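### The protocol claims power for multivariate analysis of survival that it never calculated and that its own Limitations section puts in doubt; 250 to 300 events would miss moderate associations more often than find them

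*Protocol article*

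**What the plan says.** The Sample size section opens: "As this is an observational study with no intervention, we have not conducted a power calculation". It then gives a recruitment forecast from earlier work, "we estimate that we will enroll at least 250 to 300 eligible cardiac arrest events", and concludes that this would be a large dataset "with significant power to enable exploration of important correlations between performance and survival through multivariate analysis".

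Outcomes assessment names the endpoint: "The primary outcome is survival at hospital discharge". Study aims makes the central questions ones of association, "focusing on the influence of ventilation parameters (intubation or not during resuscitation and controlled or uncontrolled ventilation", and adds post-resuscitation measures as a second group of exposures.

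The Limitations section says that, because paediatric arrest is rare, "it might be difficult to find statistically significant differences in some parameters such as mortality". It also concedes that the separate effect of any one factor may be very hard to isolate.

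**The concern.** The paragraph states as fact a property that it says was not calculated. The Limitations section then casts doubt on that property for the same endpoint, since mortality to discharge is one minus survival to discharge. It also casts doubt on it for the same task, since isolating individual factors is what a multivariate analysis is for.

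What is at stake is how null results are read. The article focuses on ventilation during resuscitation, and its Discussion expects the results to feed into international recommendations. If the protocol is on record as well powered, a non-significant result for such a factor can be taken as evidence of no association when the data could not have excluded a sizeable one.

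**Working it through.** **The plan's own figure.** There is nothing to reproduce. The 250 to 300 is a recruitment forecast, and no power, alpha, effect size or survival rate accompanies it.

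**Inputs from the document.** N = 250 and N = 300 events; a binary primary outcome; association questions on exposures such as intubation.

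**Inputs assumed, because the document gives none.** Overall survival p of 30 to 70%; share exposed s of 10 to 50%; two-sided 5% (z = 1.96); 80% power; events independent; no covariate adjustment.

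**Formula.** With n1 = sN exposed and n0 = (1 − s)N unexposed, and p = s·p1 + (1 − s)·p0 held fixed:

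- SE0 = √[p(1 − p)(1/n1 + 1/n0)]
- SE1 = √[p1(1 − p1)/n1 + p0(1 − p0)/n0]
- power = Φ[(|p1 − p0| − 1.96·SE0)/SE1]

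**Power for 45% against 35% survival, even split.**

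- N = 250 (125 per group): SE0 = √(0.48/125) = 0.0620; SE1 = √(0.475/125) = 0.0616; power = Φ[(0.100 − 0.1215)/0.0616] = Φ(−0.35) = 36%.
- N = 300 (150 per group): SE0 = √(0.48/150) = 0.0566; SE1 = √(0.475/150) = 0.0563; power = Φ[(0.100 − 0.1109)/0.0563] = Φ(−0.19) = 42%.

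**Smallest detectable odds ratio at 80% power.** Worked case: N = 250, p = 40%, s = 50%. Solving gives p1 = 0.4865 and p0 = 0.3135, a difference of 17.3 points, so OR = (0.4865/0.5135)/(0.3135/0.6865) = 2.07. At N = 300 the difference is 15.8 points and the OR 1.94. Repeating this over survival of 30 to 70%:

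| Share exposed | N = 250 | N = 300 |
|---|---|---|
| 50% | 2.04–2.19 | 1.92–2.04 |
| 20% | 2.43–3.00 | 2.25–2.68 |
| 10% | 3.25–5.39 | 2.93–4.38 |

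The survival range covers both directions of effect: a harmful factor at 40% survival has the same detectability, as an odds ratio for death, as a beneficial one at 60% survival.

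**Effect of the simplifications.** Covariate adjustment can be approximated by replacing N with N(1 − R²), where R² is the share of the exposure's variance explained by the other covariates. With R² assumed at 0.1 to 0.3, survival of 40 to 50% and an even split, the detectable OR becomes 2.12–2.40 (N = 250) or 1.99–2.22 (N = 300). Two further features reduce the information. Events rather than children are counted, and Patient eligibility says "Subsequent episodes of CA may be included for the same individual". Events are also clustered by hospital. The document gives nothing from which to size either effect, so no figure is put on them.

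**Continuous predictors.** Blood pressure or temperature do better per standard deviation. With ln(OR) = (1.96 + 0.84)/√[N·p(1 − p)] and p = 40%, N = 250 gives 2.80/√60 = 0.36, OR about 1.44; N = 300 gives 2.80/√72 = 0.33, OR about 1.39.

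**Precision of overall survival.** At 40%, 1.96·√(0.24/N) = 6.1 points (N = 250) or 5.5 points (N = 300).

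**The case against.** The best defence is that nothing hangs on the phrase. The sentence speaks of exploration, the number is a forecast with a lower bound, no test or threshold is built on it, and the Limitations section already tells the reader to expect difficulty. That lowers the likely harm but does not support the claim. Nor does the lower bound rescue it: no larger number is planned, and 80% power for 45% against 35% at an even split needs (1.96·√0.48 + 0.84·√0.475)²/0.10² ≈ 376 per group, about 752 events.

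Four stronger readings are tempting, and the document does not bear them out.

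- A reader might infer that omitting a power calculation is the error. A registry may reasonably go without one; the fault lies in claiming power afterwards.
- A reader might infer an arithmetic mistake. There is no calculation to be wrong; the statement is unsupported and inconsistent.
- A reader might infer that Limitations flatly denies the power claim. It is hedged and refers to some parameters only, so the two passages are in tension rather than exact opposites.
- A reader might infer from the long list in Table 1 that the models will be overfitted. Table 1 lists fields collected, not model terms. How many terms enter a model, and how they are chosen, is commonly left to the analysis plan, which is not shown.

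It is also fair to say that the odds ratios above rest on assumptions. The conclusion does not depend on a particular survival rate, however: at an even split the detectable value stays between 1.92 and 2.19 across the whole range.

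**Conclusion.** The concern holds as an unsupported and internally inconsistent statement. Under the stated assumptions the planned number is adequate for large effects of common binary factors (power for an OR of 2.0 at an even split and 40 to 50% survival is 76–78% with 250 events and 83–85% with 300). It is inadequate for moderate ones (35–36% and 40–42% for an OR of 1.5), and weak for factors present in a minority of events. For binary factors these are favourable figures, since adjustment, repeat arrests and clustering all worsen them; continuous predictors are detectable at smaller odds ratios per standard deviation. A general claim of power for multivariate analysis of survival therefore cannot stand as written.

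**What to change.** In Sample size, delete the power claim and put in its place:

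- the expected precision of overall survival, about ±5.5 to 6 points at an assumed 40%;
- the detectable odds ratios by exposure prevalence, with survival rate, alpha, power and independence labelled as assumptions, and a note that repeat arrests, hospital clustering and adjustment would worsen them;
- a sentence saying that the factor analyses are exploratory, will be reported as estimates with confidence intervals, and that a non-significant result will not be read as evidence of no association.

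Then make the paragraph agree with Limitations. The cost is one reworded paragraph and a less favourable stated figure. No extra patients or data are needed, and model-term limits can stay with the analysis plan.

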## Discussion

Multicenter collaborative studies are needed in order to assess the gaps in knowledge surrounding pediatric cardiac arrest. Our group as well as others, have developed collaborative platforms to this effect, demonstrating that this approach is feasible and useful [3, 20–22]. These experiences have identified those areas that need further assessment. This is the reason for the creation of a registry of in-hospital CA in childhood in European and Latinamerican countries. Its development will provide access to CPR data in different hospital settings. This data gathering from different countries and hospitals might enlighten the analysis of compliance with the actual guidelines in these countries and the identification of barriers in treatment of pediatric cardiac arrest. Multicenter international collaboration in Spanish and English will allow the investigators to recruit more patients and enable the analysis of current controversies in the treatment of pediatric CA and post-resuscitation care. We expect the results to contribute to the development of further international recommendations.

## Limitations

The main limitation of the study is that patient recruitment cannot be planned because CA is an unexpected sudden event. On the other hand, when CA happens, all attention is driven towards CPR, so it might be difficult to record all data related to the characteristics of CPR while performing it. Another limitation of the study is that the final results of CPR are influenced by many variables and it can be very difficult to differentiate the isolated effect of each factor. Furthermore, recording as many variables as aimed per CA requires a lot of dedication and careful review and supervision of each case by the study coordinator. Being CA a rare event in pediatric patients, it might be difficult to find statistically significant differences in some parameters such as mortality. Thus, the participation of a significant number of hospital centers and collaborating researchers is necessary. This is one of the fundamental reasons for a multicenter study. Finally, the neurological follow-up at one year of some patients will end after the end of the study period.

## Data Availability

Not applicable.

## Abbreviations

PACHIN: Pediatric In-Hospital Cardiac Arrest International Registry
CA: Cardiac arrest
CPR: Cardiopulmonary resuscitation
IHCA: In-hospital cardiac arrest
ROSC: Return of spontaneous circulation
ECMO: Extracorporeal circulatory support
ILCOR: International Liaison Committee on Resuscitation
IQR: Interquartile range
SD: Standard deviation
CONSORT: Consolidated Standard of Reporting Trials
